##### *Adverse experiences*

Adverse experiences will be tabulated using MedDRA preferred terms. The number and percentage of participants experiencing each specific adverse experience will be tabulated by severity and by relationship to treatment. For the calculations in these tables, each participant's adverse experience will be counted once under the maximum severity or the strongest recorded causal relationship to study product.

A listing of expedited adverse events reported to the DAIDS Safety Office will provide details of the event including severity, relationship to study product, onset, duration, and outcome.

##### *Local laboratory values*

Boxplots of local laboratory values will be generated for baseline values and for values measured during the course of the study. Each boxplot will show the 1st quartile, the median, and the 3rd quartile. Outliers, or values outside the boxplot, will also be plotted. If appropriate, horizontal lines representing boundaries for abnormal values will be plotted.

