The VRC 004 study was a Phase I randomized, placebo-controlled, dose-escalation study of the 4-plasmid DNA vaccine, VRC-HIVDNA009-00-VP. Unblinded results indicated that dosages of DNA vaccines up to 8 mg are safe and well-tolerated. The 4 mg dose was chosen for further evaluation as administration in a three vaccination schedule resulted in a promising immune response that is easier and less costly to administer than the 8 mg dose. Adverse events possibly related to vaccination included one case each of urticaria (grade 3), maculopapular rash (grade 2), and transient, asymptomatic neutropenia (grade 3); all resolved without sequelae.

The reactogenicity of the DNA vaccine at the 4 mg dosage, as reported in the final VRC 004 diary cards, is shown in Table 4-2. Malaise, myalgia, and/or headache were the most frequently recorded systemic symptoms and were also those included in the “moderate” severity systemic reactogenicity reported by 20% of subjects. Pain was the only local symptom reported as moderate in severity by some subjects.

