Protocol VRC 006 was conducted by the VRC Clinic and was the first Phase I, randomized, placebo-controlled dose escalation study to evaluate the Ad5 vaccine as a single agent. The unblinded study data indicates that the vaccine is safe for healthy subjects at the three dose levels evaluated. There were no serious adverse events attributed to study vaccine. There were three grade 2 (moderate) adverse events possibly related to vaccination including: 1) asymptomatic neutropenia noted 21 days after study injection in subject with prior history of low neutrophil counts; 2) diarrhea (duration one day) on the third day after study injection and 3) asymptomatic steatohepatitis (fatty liver) which was evaluated by a hepatologist as likely to be a pre-existing condition. When administered as a single agent in VRC 006, the 10^9 and 10^10 PU doses were associated with less reactogenicity than the 10^11 PU dose. At the 10^10 PU dose, none of the subjects had fever and the other reactogenicity was mild or none. At the 10^11 PU dose, four subjects had a flu-like set of symptoms that may include fever,

headache, muscle aches, malaise, and chills starting within 24 hours after vaccination and lasting several hours. Symptoms may be up to moderate in severity.

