#### Laboratory

**Neutralizing antibody titers of Ad5**  $\geq 1:12$  (for 90% neutralizing activity)

**Hemoglobin**  $\geq$  sex-specific institutional lower limit of normal and at least 11.0 g/dL for women, 12.5 g/dL for men

**WBC count** = 3,300 to 12,000 cells/mm^3

**Total lymphocyte count**  $\geq 800$  cells/mm^3

**Remaining differential** either within institutional normal range or accompanied by site physician approval

**Platelets** = 125,000 to 550,000/mm^3

**ALT** is less than 1.25 times the institutional upper limit of normal

**Creatinine** does not exceed institutional upper limit of normal

**Negative HIV-1/2 blood test.** US participants must have a negative FDA-approved EIA. Non-US sites will use locally available and locally approved assays.

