### 8.3 Endpoints

#### 8.3.1 Safety

Assessment of product safety will include clinical observation and monitoring of hematological and chemical parameters. Safety will be evaluated by monitoring participants for local and systemic adverse reactions after each injection and for 12 months after the first injection.

The following parameters will be assessed:

- Local reactogenicity signs and symptoms
- Systemic reactogenicity signs and symptoms
- Laboratory measures of safety
- Adverse events

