**Table 8-1 Probability of response for different safety scenarios**

| True event rate (%) | Pr(0/30) | Pr(2+/30) |
|---------------------|----------|-----------|
| 1                   | 0.740    | 0.036     |
| 3.5                 | 0.343    | 0.283     |
| 5                   | 0.215    | 0.446     |
| 10                  | 0.042    | 0.816     |
| 20                  | 0.001    | 0.989     |
| 30                  | <0.001   | >0.999    |
| 40                  | <0.001   | >0.999    |

An alternative way to describe the statistical properties of the study design is in terms of the 95% confidence interval about the event rate that would be obtained from the observed safety data. Table 8-2 shows the exact 2-sided 95% confidence intervals for the probability of an event based on a particular observed proportion. If none of the 90 participants receiving a vaccine regimen experience a safety event, the 95% exact 2-sided upper confidence bound for the rate of such events in the total vaccinated population is 4%. Restricted to any of the individual vaccine arms (n=30), the exact 2-sided upper confidence bound for this rate is 12%.

**Table 8-2 Exact 2-sided 95% confidence intervals based on observing a particular proportion of safety endpoints for arms of size n1 and n2**

| Observed proportion | Confidence interval (%) |
|---------------------|-------------------------|
| 0/30                | [0.0,11.6]              |
| 1/30                | [0.1,17.2]              |
| 2/30                | [0.8,22.1]              |
| 0/overall 90        | [0.0,4.0]               |
| 1/overall 90        | [0.0,6.0]               |
| 2/overall 90        | [0.3,7.8]               |

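### Section 8.5.3 summarises measured laboratory values by boxplots alone, so a graded change is counted only if the site records it as an adverse event, and never against its baseline grade

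*Protocol*

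**What the plan says.** Section 8.3.1 names four safety parameters and lists "Laboratory measures of safety" as an item separate from adverse events. Section 8.5.3 then gives each parameter its analysis:

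- **Reactogenicity:** count and percentage of participants by severity, once per participant at the worst grade.
- **Adverse experiences:** count and percentage by MedDRA preferred term, severity and relationship, again once per participant.
- **Local laboratory values:** "Boxplots of local laboratory values will be generated for baseline values and for values measured during the course of the study". Each plot shows the quartiles and median. "Outliers, or values outside the boxplot, will also be plotted". Limits of abnormality are optional: "If appropriate, horizontal lines representing boundaries for abnormal values will be plotted".

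Section 8.4.1 frames the safety question as participants with an event out of 30 per arm or 90 overall: "Table 8-2 shows the exact 2-sided 95% confidence intervals for the probability of an event based on a particular observed proportion". Section 11.1 says the screening assessments serve as the baseline for comparing safety data. Section 8.6 says that participants and site staff are not blinded.

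**The concern.** Laboratory values are the only one of the four parameters whose planned summary has no numerator. In arms of 30, laboratory toxicity would most plausibly appear as a shift in one or two people, and a boxplot handles that poorly. The box stays where it is, and the affected participants appear as isolated points with no link to where they started.

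The link to baseline has a practical use here. Table 6-1 fixes limits for total white cells and lymphocytes, but the rest of the differential, which would include neutrophils, need only be "either within institutional normal range or accompanied by site physician approval". Someone can therefore enter with a value outside the normal range. Section 4.2.1 describes such a situation with the Ad5 vaccine: "asymptomatic neutropenia noted 21 days after study injection in subject with prior history of low neutrophil counts". On baseline and follow-up boxplots, a low point after vaccination could be an entry value carried forward or a new fall.

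At stake is whether the first primary objective, safety by route of boost, has a laboratory rate that rests on the measurements themselves. The alternative is a rate that rests on each site's decision to write up an adverse event.

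**Working it through.** **1. The plan's own figures.** Table 8-1 follows from the binomial with n = 30. At a true rate of 5%, P(0) = 0.95^30 = 0.215, and P(2 or more) = 0.446, as printed. The other rows reproduce as well. Table 8-2 follows from the exact (Clopper-Pearson) interval, with lower limit the 0.025 quantile of Beta(x, n − x + 1) and upper limit the 0.975 quantile of Beta(x + 1, n − x). All six rows reproduce.

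**2. Expected counts in one arm.** The protocol gives no expected rate for a graded laboratory change, so 5% is an assumption.

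- P(0) = 0.215
- P(1) = 30 × 0.05 × 0.95^29 = 0.339
- P(2) = 435 × 0.05² × 0.95^28 = 0.259
- Sum = 0.81

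Over an assumed range of 2% to 5%, the chance of at least one case in 30 runs from 0.455 to 0.785. The chance of two or more runs from 0.121 to 0.446.

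**3. What a boxplot does with such counts.** A quarter of 30 is 7.5 participants. One or two changed values leave the quartiles and median essentially where they were. The values may be plotted as outliers, but they are neither counted nor paired with a screening value.

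**4. What a count would give.**

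| Participants whose grade rises | Percentage | Exact 95% CI |
|---|---|---|
| 0/30 | 0% | 0.0% to 11.6% |
| 1/30 | 3.3% | 0.1% to 17.2% |
| 2/30 | 6.7% | 0.8% to 22.1% |

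These are the intervals already in Table 8-2.

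**5. Where a laboratory abnormality could be counted at present.** Section 13.3 requires adverse events to be sent to the data centre but does not say which graded laboratory values must become adverse events. Table 13-2 reaches laboratory abnormalities only at Grades 3 and 4, and Section 13.3.1 counts them only if judged related to vaccine. The Ad5 case in Section 4.2.1 was grade 2, so it would not trigger that table. Nothing in the adverse experience summary records the baseline grade.

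**6. Blood draws available.** Appendices B and C schedule the blood count, ALT and creatinine at screening, D14, D42, D70, D175 and D273. D70 is the last draw before the D168 boost. It falls 70 − 56 = 14 days after the third DNA dose and 168 − 70 = 98 days before the boost. The post-boost draws fall 175 − 168 = 7 and 273 − 168 = 105 days after it.

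**The case against.** The strongest reply is that a count already exists. The adverse experience tables in Section 8.5.3 would include neutropenia recorded as an adverse event. Section 13.3.1 introduces the contents of Table 13-2 as adverse events, Section 13.5.2 words a laboratory abnormality as one kind of adverse event, and both earlier neutropenia cases (Sections 4.1.1 and 4.2.1) were reported that way. This stands. A reader might infer from the boxplot plan that neutropenia would have no rate by route, and the documents do not support that. What remains is that the count depends on a recording decision with no stated rule, made by staff who know the route.

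A reader might also take the two earlier cases as an established laboratory signal. The documents do not support that either. They are isolated: one grade 3 with DNA and one grade 2 with Ad5. Section 4.2.2 reports no significant differences between groups in blood counts, liver enzymes or creatinine in the placebo-controlled Ad5 trial.

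Nor is the distinction between pre-existing and new abnormalities wholly neglected. Adverse event collection starts at Day 0 (Appendix C). Section 13.7 lists reports on pre-existing conditions and on the white cell differential, and Section 13.7.2 has out-of-range values reviewed. These are monitoring tools, however, and no planned summary by arm comes from them.

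Finally, shift tables are often left to a statistical analysis plan, which is not at hand. That lowers the urgency. The point is still open to comment because the protocol does name a summary for laboratory values, and that summary cannot yield a proportion.

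**Conclusion.** The point holds in a limited form. For measured laboratory values the protocol specifies a summary that cannot count participants with a graded change or show whether the change is new. The adverse event route fills the gap only in part, because it depends on unblinded site judgement and carries no baseline grade. No figure in the protocol is wrong, and no bias in recording is shown; the open-label design only makes it possible.

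The practical size is one or two participants per arm, whose rate would otherwise rest on whether a form was completed. The 2% to 5% range behind that statement is an assumption, but the conclusion does not depend on the exact value: any rate that produces only a few cases in 30 leaves the boxplot summary essentially unchanged. This is an inexpensive improvement of modest priority.

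**What to change.** Keep the boxplots and add one table to Section 8.5.3. For the blood count with differential, platelets, ALT and creatinine, grade each value with the DAIDS table already used in the trial. Tabulate by arm the worst post-baseline grade against the screening grade. Give the number, percentage and exact 95% confidence interval for participants whose grade rises.

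Repeat the table for the post-boost draws at D175 and D273, with D70 as the pre-boost reference. State that D70 is the last draw before the boost and an imperfect reference, because it follows the third DNA dose by 14 days. State also that no blood count is scheduled between 7 and 105 days after the boost, so the table cannot describe that interval, which includes the 21 days at which the earlier Ad5 case was noted.

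The cost is one table from data already collected, with no added samples or visits. The downside is that many cells will hold 0 or 1 and must be read with their wide intervals.

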#### **8.5.4 Immunogenicity analysis**

For the statistical analysis of immunogenicity endpoints, all data from enrolled participants will be used according to the initial randomization assignment regardless of how many injections they received. The only exception will be to exclude data from HIV-infected

participants at or post infection. Thus, for HIV-infected participants, only immunogenicity data from samples drawn prior to HIV infection will be included in the analysis.

If assay data are qualitative (i.e., positive or negative), then analyses will be performed by tabulating the frequency of positive response for each assay by arm at each time point that an assessment is performed. Binomial response rates will be presented with their corresponding exact 95% confidence interval estimates.

To compare the response rates of any two vaccine arms, a significant difference will be declared if the 2-sided 95% confidence interval for the difference in response rates between the two arms excludes 0. If assays are run at multiple time points, the probability of observing at least one positive response by a given time point and the probability of observing more than one response by a given time point will be estimated, with corresponding confidence intervals, for each vaccine arm using maximum likelihood based methods [53]. Missing responses will be assumed to be missing at random (i.e., conditional on the observed data the missingness is independent of the unobserved responses).

For continuous assay variables, overall differences between arms at a specific time point will be tested by a 2-sample t-test if the data appear to be normally distributed after certain power or logarithm transformations, or by utilizing the nonparametric Wilcoxon rank sum test if the transformed data are not normally distributed. More sophisticated analyses employing repeated measures methodology (for example, repeated measures ANOVA or generalized estimating equations) may be utilized to incorporate immune responses over several time points. However, inference from such analyses would be limited by the small sample size of this study. All statistical tests will be 2-sided and will be considered statistically significant if  $p \leq 0.05$ . Graphical descriptions of the longitudinal immune responses will also be given.

Some immunologic assays have underlying continuous or count-type readout that is often dichotomized into responder/nonresponder categories. For these assays, graphical and tabular summaries of the underlying distributions will be made. These summaries may be performed on transformed data (e.g., log transformation) to better satisfy assumptions of symmetry and homoscedasticity. If arm comparisons in these underlying distributions reveal that differences are best summarized as a shift in the location of the distribution, then results will be presented in the form of arm means (or medians) with associated confidence intervals and statistical tests for differences between arms as described above. If arm comparisons in these underlying distributions reveal that differences are best summarized by a mixture model (i.e., responder and nonresponder subgroups are clearly identifiable), then results will be presented in the form of response rates with associated confidence intervals and statistical tests as described above. In addition, Lachenbruch's test statistic [54] will be used for evaluating the composite null hypothesis of equal response rates in the two arms and equal response distributions among responders in the two arms. This test statistic equals the square of a binomial Z-statistic for comparing the response rates plus the square of a Wilcoxon statistic for comparing the response distributions in the subgroup of responders. A permutation procedure is used to obtain a 2-sided p-value.

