Preexisting immunity to adenovirus serotype 5 may decrease immune responses to recombinant adenoviral serotype 5 vaccines [20,21]. Including both participants who are seropositive and participants who are seronegative for Ad5 neutralizing antibodies in this trial would likely be a confounding factor in comparing different routes of administration. To more closely reflect the situation in areas of the world most affected by HIV where 75-99% of the population are seropositive for Ad5 neutralizing antibodies [22], only volunteers possessing detectable levels of neutralizing antibodies against Ad5 (titer  $\geq 1:12$  for 90% neutralizing activity) will be enrolled (Table 6-1).

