#### 8.4.2 Sample size calculations for immunogenicity

The main goal of this trial regarding immunogenicity is to determine if ID or SC route of administration of the Ad5 boost is superior to IM administration in eliciting vaccine-induced HIV-specific T cell responses. Because IM administration is easier to administer, IM administration would continue to be used with this product unless there is a large improvement in immune response. The immunogenicity outcomes involve both preliminary estimation and a formal comparison of the mean magnitude of T-cell responses among study groups. Since the standard error of the estimated mean response magnitude depends on the true population variance, several parameters for the sample size calculations for immunogenicity will be estimated from existing ELISpot assay data.

It has been observed from previous HVTN studies that the magnitude of T-cell responses assessed by the IFN- $\gamma$  ELISpot assay appears to be normally distributed after a logarithm transformation. Since logarithm transformations are more intuitive for interpreting fold differences, log-10 transformation will be adopted in the estimation of distribution parameters of the true underlying population distribution.

Consider the sample standard deviation to be 0.35 after log-10 transformation. Two-sided confidence intervals for the mean magnitude of the T-cell responses based on observing a particular mean magnitude of responses can be found in Table 8-3 for groups of size 30 and 27, accounting for 10% missing immunogenicity data.

**Table 8-3 Two-sided confidence intervals for the T-cell response based on observing a particular mean response magnitude in the vaccinees (n=30,27)**

| Observed mean magnitude* | 95% CI (n=30) | 95% CI (n=27) |
|--------------------------|---------------|---------------|
| 100                      | [75,134]      | [74,136]      |
| 150                      | [113,201]     | [111,204]     |
| 200                      | [150,267]     | [148,272]     |
| 250                      | [188,334]     | [185,339]     |
| 300                      | [225,401]     | [222,407]     |
| 350                      | [263,467]     | [259,475]     |
| 400                      | [300,534]     | [296,543]     |
| 450                      | [338,601]     | [333,610]     |
| 500                      | [375,668]     | [369,678]     |

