\*Observed SFU per ELISpot well ( $\sim 2 \times 10^5$  PBMC). Response rates conventionally reported per  $10^6$  PBMC.

A formal comparison of the immunogenicity between the study groups (n=30) will also be performed. For example, a 2-fold difference in mean response magnitudes between two groups of size 30 is detectable with 82% power for a two-sided two-sample t-test with a Type I error rate of 0.05. Based on groups size of 30 and a sample standard deviation of 0.35 after log-10 transformation, additional power calculations for comparison of mean response magnitudes between arms that can be distinguished with statistical power of 80% and 90% are provided in Table 8-4. This calculation accounts for 10% of enrolled participants having missing data for the primary immunogenicity endpoints. Note that the sizes of differences that the trial is powered to detect are fairly large.

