#### **8.5.4.1 Missing data**

If the probability of missing immunogenicity measurements depends on either covariates or on the immunogenicity outcomes of participants, then the methods described above may give biased inferences and point estimates. If a substantial amount of immunogenicity data is missing (at least 1 value missing from more than 20% of participants), then secondary analyses of the immunogenicity endpoints will be conducted using methods that relax the missing completely at random assumption to a missing at random assumption. For a univariate binary and quantitative outcome, respectively, a generalized linear model with a

binomial or normal error distribution will be used for estimation and testing. For assessing repeated immunogenicity measurements, generalized estimating equations models with multiple imputation of missing responses will be used. The models will include as covariates all available baseline predictors of the missing outcomes. The longitudinal models will also include all observed immunogenicity data.

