### **8.6 Randomization of treatment assignments**

The randomization sequence will be obtained by computer-generated random numbers and provided to each HVTU by the SDMC using the procedures described in the HVTN MOP (Study Operations>Enrollment>Randomization). At each institution, the pharmacist with primary responsibility for drug dispensing is charged with maintaining security of the randomization list. The randomization will be done in blocks to ensure balance across arms. Participants and site staff will not be blinded as to the group assignment.

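### The primary ELISpot comparison is fixed as an unadjusted two-sample test, although screening Ad5 titer and Day 70 ELISpot are collected and could sharpen it at little cost

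*Protocol*

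**What the plan says.** Section 8.5.4 sets the test for assays with a continuous readout: "overall differences between arms at a specific time point will be tested by a 2-sample t-test if the data appear to be normally distributed". The data may be transformed first, and a Wilcoxon rank sum test is used otherwise. The primary endpoint, ELISpot magnitude four weeks after the boost (Day 196), falls under this rule. Repeated-measures models are optional there. Section 8.4.2 powers the trial on the same test: "a 2-fold difference in mean response magnitudes between two groups of size 30" is said to be "detectable with 82% power for a two-sided two-sample t-test with a Type I error rate of 0.05".

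Section 1.3 says "Preexisting immunity to adenovirus serotype 5 may decrease immune responses to recombinant adenoviral serotype 5 vaccines". The design response is to enroll only participants with a titer of at least 1:12 (Table 6-1). No upper limit is given. Section 8.6 says "The randomization will be done in blocks to ensure balance across arms" and states no stratification by titer.

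Appendix B shows Ad5 antibody at screening and ELISpot at Day 0, Day 70 and Day 196. All groups receive the same DNA product at Days 0, 28 and 56, and differ only from the Day 168 boost.

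Covariates appear only in Section 8.5.4.1, in secondary analyses that run if there is "at least 1 value missing from more than 20% of participants".

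**The concern.** The protocol itself treats Ad5 immunity as a driver of response. Section 2.2 reports that ELISpot response rates in earlier Ad5 vaccine trials ran from 43% to 91%, depending on dose and titer. Restricting entry to seropositive participants removes the contrast between seropositive and seronegative, but leaves the range above 1:12 open. The primary test does not use the measured titer. Nor does it use Day 70 ELISpot, which is the same assay applied to the primed response that the boost acts on.

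With about 27 evaluable participants per arm, any outcome variance that these two values explain stays in the error term, and a chance imbalance in titer goes unadjusted. Section 8.4.2 itself notes that only fairly large differences are detectable. At stake is precision of the ID/IM and SC/IM comparisons, obtainable without new procedures.

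**Working it through.** **Inputs**
- Difference: 2-fold, log10(2) = 0.301 (Section 8.4.2).
- SD: "Consider the sample standard deviation to be 0.35 after log-10 transformation".
- Evaluable per arm: 30 × 0.9 = 27. Section 8.4.2 says "This calculation accounts for 10% of enrolled participants having missing data for the primary immunogenicity endpoints".
- Two-sided alpha 0.05 (Sections 8.4.2 and 8.5.4).
- R-squared of the two covariates together: not in the protocol, so ranged from 5% to 40%.

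**The plan's own figure.** The standard error of the difference is 0.35 × √(2/27) = 0.0953, and the noncentrality is 0.301/0.0953 = 3.16. The noncentral t on 52 df gives power 87.3% (90.6% with 30 per arm). The stated 82% is not reproduced. A normal approximation at alpha 0.025 with 27 per arm gives 82.1% (t-based 80.0%), but the protocol states 0.05. That mismatch is a separate matter; 87% is the baseline used here.

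**With adjustment.** Residual SD = SD × √(1 − R²), with 2 df lost. Equivalent unadjusted n per arm = 27/(1 − R²).

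| Assumed R² | Residual SD | Power, 2-fold | Fold detectable at 80% power | Equivalent n per arm |
|---|---|---|---|---|
| 0 (unadjusted) | 0.350 | 87.3% | 1.87 | 27.0 |
| 5% | 0.341 | 88.9% | 1.84 | 28.4 |
| 10% | 0.332 | 90.4% | 1.81 | 30.0 |
| 25% | 0.303 | 94.7% | 1.72 | 36.0 |
| 40% | 0.271 | 97.9% | 1.63 | 45.0 |

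**If the SD is larger.** The Env A interval in Table 3-2 (log10 scale, 1.45 to 2.12, n = 10), read as t-based, implies SD = 0.335 × √10 / 2.262 = 0.47. That is Ad5 alone, a different regimen, so it serves only as a sensitivity value. Power at SD 0.47 is 63.7% unadjusted, and 68.2%, 76.0% and 84.6% at R² of 10%, 25% and 40%.

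**If the covariates predict nothing.** Chance imbalance in two covariates inflates the variance by about 1 + 2/49 = 1.041. Power then falls from 87.3% to 85.9%. The adjusted figures above do not include this inflation, so they are slightly optimistic. Break-even is at R² of about 1 − 1/1.041 = 4%. With eight uninformative terms, as several site indicators could add, the same calculation gives about 81%.

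**Is Day 70 admissible?** It follows randomization. However, the arms are treated identically until Day 168, so the boost route cannot affect it. It precedes the boost by 168 − 70 = 98 days (14 weeks), so it measures the primed response, not the level immediately before the boost.

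**The case against.** The strongest reply is that nothing here is wrong. A two-sample test in a randomized trial is valid and controls type I error, chance imbalance in titer included. It also matches the test used for the power statement. Section 1.3 describes confounding from mixing seropositive and seronegative participants, and the entry criterion removes that mix. All of this stands. Against it, the protocol does fix the primary test without covariates.

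A reader might go further in four ways that the documents do not support:
- **That known outcome variance is being left in the error term.** Only Ad5 titer has any documented link to response, and that link is qualitative. Nothing shows how much titer explains among seropositive participants, or that Day 70 ELISpot or site predicts Day 196.
- **That adjustment lifts power from 80% to 91%.** This pairs alpha 0.025, which the plan does not state, with an assumed R² of 25%. At the stated alpha the same R² gives 87% to 95%.
- **That the covariate analysis needs twice the planned missing data.** The 20% trigger counts participants with any missing immunogenicity value, whereas the 10% concerns the primary endpoint alone. Independent 10% missingness at three visits would give 1 − 0.9³ = 27%, already above the trigger.
- **That site must be in the model, or that titer is certainly unstratified.** The number of sites is not stated, and many site terms could cost power. Section 8.6 is silent on stratification and refers procedures to the network's manual of operations.

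Adjustment also has practical gaps to close. Missing Day 70 values could drop participants from the model, and low values need a rule before taking logs. In Table 3-1, 5 of 19 participants had no positive ELISpot response to any pool after DNA alone.

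**Conclusion.** The point holds as one of efficiency. The protocol fixes an unadjusted primary comparison while collecting two legitimate covariates, one of which it names as likely to affect response. At the stated inputs the gain is about 2 to 11 percentage points of power (87% to between 89% and 98%) for R² of 5% to 40%. At SD 0.47 it is about 5 to 12 points for R² of 10% to 25%. These figures rest on the assumed R² and on a normal model for log10 magnitude. Below an R² of about 4%, adjustment gains nothing and could cost up to about 1.4 points. It is a worthwhile improvement, and leaving it out does not invalidate the trial's inference.

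**What to change.** Prespecify the primary analysis as a linear model of log10 Day 196 ELISpot magnitude on arm, log10 screening Ad5 titer and log10 Day 70 ELISpot magnitude. State with it:
- a fixed floor for zero or background values, applied before taking logs;
- a simple imputation for missing Day 70 values that does not use the outcome or the arm, such as the pooled mean of observed log10 values, so that no participant with a Day 196 value is dropped;
- site only as a pooled region term, if at all;
- reporting of adjusted ID/IM and SC/IM ratios of geometric means with confidence intervals.

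Run this model whatever the amount of missing data. Keep the unadjusted t-test, the Wilcoxon test and the Lachenbruch two-part test of Section 8.5.4 as sensitivity analyses; the last covers the case of a clear split into responders and nonresponders.

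The cost is a change of wording and a few degrees of freedom. No blood draw or assay is added.
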